### Sample size

As this is a pilot trial the primary outcome is understanding the feasibility of implementing a large-scale trial. However, to determine sample size for sufficient power to evaluate developmental trajectories of our secondary outcome variables population estimates were derived using data from Beck et al. [42] who had the same design, population and outcome (quality of life by means of EQ-5D-3 L) as in the present study and showed a significant difference between intervention and control group in the EQ-5D-3 L follow-up score of (0.758 [0.222] versus 0.534 [0.355], (*P* = 0.001). Here it was found that the variation seen in quality of life was due to residual variation (the variation from individual to individual) and was not dependent on the clusters. Hence, with a statistical significance level of 0.05 and a power of 80% app. 53 is needed in each group. Estimating a drop-out rate of 20%, due to a longer intervention period than the former study [42], app. 130 participants are needed. This number could probably be included in approximately 10 weeks, for respectively control and intervention group.

The sample size for this trial will be compared with the actually collected samples as to estimate the required sample size for a future cluster randomized trial.

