#### Secondary outcomes

EuroQol-5D-3 L (EQ-5D-3 L) will be used to measure health related quality of life, which is the primary outcome (at *t* = 0, *t* = 1, *t* = 2). EQ-5D-3 L is a standardized instrument for use as a measure of health outcome and is recommended by the Danish National Board of Health [26–28]. The EQ-5D-3 L descriptive system comprises the following 5 dimensions (5D): Mobility, self-care, usual activities, pain/discomfort, and anxiety/depression. Each dimension has 3 levels (3 L): No problems, some problems, extreme problems. The raw score must be converted to an EQ-5D-3 L score ranging from 1.000 to − 0.624 [29]. Permission to use EQ-5D-3 L has been obtained from www.euroqol.org/.

Thirty-second chair-stand, recommended by the Danish National Board of Health [26–28] will be used to measure muscle strength (at *t* = 0, *t* = 1, *t* = 2). Participants are asked to fold their arms across the chest and to stand up and sit down on a chair without pushing off with arms, as many times as possible for 30 s. The arms may be used for assistance or for safety if need [30]. The height of the chair and mode of chair stand will be registered.

Nutritional status will be assessed by means of weight, height, and BMI (at t = 0, t = 1, t = 2). Weight (in kg to the nearest decimal) is measured (with participants wearing light indoor clothes) on calibrated project weights. As measurement of height is often not feasible in this old and frail population with chronic disease, data of height will also be retrieved from self-reported height. BMI is calculated as actual weight in kilograms divided by the square of height in meters.

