#### Analysis

Although this is a pilot study, we do want to explore whether or not there is a difference between groups. All statistical analysis will be performed using a statistics program (SPSS) for Windows. Data will be entered in EXCEL and will subsequently be exported into SPSS software for analysis. All participants will be included in the analysis, regardless of whether they have completed the study or not. Depending on the data type and distribution t-test, Mann-Whitney U test and Chi2 test will be used to compare changes within and between the groups. The model of data analysis needs to consider the effect of clustering; thus, this study will be using effect models with the cluster treaded as a random effect.

The intracluster correlation coefficient (ICC) for quality of life will be calculated by means of ANOVA and published to assess the appropriateness of the sample size assessment in the study.

To assess the feasibility of the outcome measurements the confidence intervals (95% CI) will be calculated to interval estimate the population.

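### The 80% power for EQ-5D-3L treats participants as independent, but the plan compares three areas with two under an area random effect; with 3 degrees of freedom the power is about 73% at best at 53 per group

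*Protocol article*

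**What the plan says.** The Sample size section of the protocol article says that feasibility is the primary outcome, and then sizes the trial for power on the secondary outcomes. It takes EQ-5D-3L follow-up scores from an earlier study, "0.758 [0.222] versus 0.534 [0.355" (closing bracket omitted here), and reports that the variation in that study "was due to residual variation (the variation from individual to individual) and was not dependent on the clusters". From this it concludes that, "with a statistical significance level of 0.05 and a power of 80" per cent, "app. 53 is needed in each group". Allowing for 20% drop-out, "app. 130 participants are needed".

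The Abstract, Trial design and Participants sections allocate five whole community care areas, three to intervention and two to control. The Analysis section says that clustering has to be taken into account and that "this study will be using effect models with the cluster treaded as a random effect". It also promises to calculate and publish the ICC for quality of life, as a check on the sample size. The Implementation section ends recruitment in each arm after 10 weeks or once the number from the power calculation is reached.

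The Secondary outcomes section says that EQ-5D-3L "will be used to measure health related quality of life, which is the primary outcome". The Abstract, the Primary outcome section and the Sample size section all make feasibility primary.

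**The concern.** The sample size and the analysis rest on different assumptions. The first sets the area effect to zero and counts individuals. The second treats area as a random effect, so the arm contrast is judged against variation between areas. Five areas in two arms leave 5 − 2 = 3 degrees of freedom for that, and the two-sided 5% critical value is 3.18 rather than 1.96. That one earlier study found no dependence on clusters does not show that the ICC is zero among these five areas. Even if it were zero, the small number of areas would still limit the test.

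The stated power has consequences. It sets the recruitment target and one of the two recruitment stopping conditions. It also supports the wish, stated in the Analysis section, to explore a difference between groups. And the pilot is meant to inform the size of a later cluster trial, so an individual-level calculation could be carried forward.

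**Working it through.** **Inputs.** From the Sample size section: means 0.758 and 0.534, with bracketed values 0.222 and 0.355 read as SDs; alpha 0.05, taken as two-sided because the article does not say; power 80%; 53 per group; drop-out 20%. From Trial design: 3 and 2 areas. The cluster in the Analysis section is read as the care area. The article gives no ICC, so 0 to 0.05 is assumed.

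**Step 1: the plan's own figure, under independence.**
- Difference = 0.758 − 0.534 = 0.224.
- Pooled SD = √[(0.222² + 0.355²)/2] = 0.296.
- n per group = 2(1.960 + 0.842)² × 0.296²/0.224² = 27.4, so 28 (29 with the t distribution).
- The stated 53 is not reproduced. Using the larger SD alone gives 40. The figure 53 appears with SD 0.355 and 90% power, which is not what the text states.
- With 53 per group and SD 0.296, power under independence is 97%.
- The difference for which 53 per group gives exactly 80% under independence is 2.802 × 0.296 × √(2/53) = 0.161.
- Drop-out: 106/0.8 = 132.5, so about 130 is a fair rounding.

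**Step 2: power of the area-level comparison.** With n evaluable per arm spread evenly over the arm's areas,

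Var = SD² × [ICC × (1/3 + 1/2) + (1 − ICC) × 2/n].

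Power comes from the noncentral t with 3 df, critical value 3.18 and noncentrality = difference/√Var. For example, at ICC 0.01 and n = 53: √Var = 0.296 × √(0.00833 + 0.03736) = 0.0633; noncentrality = 0.224/0.0633 = 3.54; power 66%.

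| ICC | 0.224, n = 53 | 0.224, n = 65 (no drop-out) | 0.161, n = 53 |
|---|---|---|---|
| 0 | 73.5% | 81% | 48% |
| 0.001 | 73% | 80% | 48% |
| 0.01 | 66% | 72% | 42% |
| 0.02 | 60% | 65% | 37% |
| 0.05 | 46% | 49% | 28% |

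With SD 0.355 in place of 0.296 (difference 0.224, n = 53), power is 59%, 52%, 46% and 35% at ICC 0, 0.01, 0.02 and 0.05. At ICC 0.05 and SD 0.296, unlimited participants in these five areas would give at most 70%.

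**Step 3: does the result depend on the exact 3-df test?** A simulation of 60,000 runs used a random-area model with Satterthwaite degrees of freedom and the area variance truncated at zero. At difference 0.224 and 53 per arm it gave 72.7% at ICC 0, 71.9% at 0.001, 65.5% at 0.01 and 45.4% at 0.05. The conclusion is the same.

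**Step 4: what drives the loss.** Keep the variance inflation but use normal quantiles in place of 3 df. At difference 0.224, power is then 97% at ICC 0, 94% at 0.01 and 90% at 0.02, and drops below 80% only at about ICC 0.044. At small ICC the shortfall is therefore due to the degrees of freedom.

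**The case against.** This is a feasibility pilot. The 80% is attached to secondary outcomes, and the Analysis section describes the comparison as exploratory in spirit. The article does not treat the absence of clustering as settled either: it commits to publishing the ICC and to revisiting the sample size for the future trial. All of this stands. It lowers the severity, but it does not make the 80% correct.

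A second argument is that 53 is generous. The printed inputs need only 28, and under independence 53 gives 97%. That slack is real and is credited in the 73.5%. If it is not credited, and 53 is taken as exactly the 80% sample size, power falls to 48% at ICC 0. Without drop-out, power at the printed effect is 81% at ICC 0 and 80% at 0.001, but the plan itself expects to lose 20%.

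A reader might infer more than the document supports:
- That a tiny ICC is what destroys the power. It is not, as Step 4 shows; the shortfall is already there at ICC 0.
- That the earlier study was too small to detect clustering. The article gives neither its size nor its number of clusters, so this cannot be said.
- That the primary endpoint is underpowered, because one sentence calls EQ-5D-3L primary. That sentence stands under the Secondary outcomes heading and conflicts with three other sections. It is a labelling error and does not make the power fault more serious.

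**Conclusion.** The 80% power claim is wrong as written, with moderate severity. Under the planned area random effect, with five areas and 53 evaluable per group, power at the printed effect is about 73% at ICC 0, 66% at 0.01, 60% at 0.02 and 46% at 0.05. If 53 is read as the exact 80% sample size under independence, it is 48% at ICC 0 and 42% at 0.01. Both readings fall short, and the article does not show which effect size 53 was meant to detect.

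This rests on reading the brackets as SDs, a two-sided 5% test, participants spread evenly over the areas within each arm, 20% drop-out as planned, and assumed ICCs. It does not follow that the pilot fails its purpose or must be enlarged. The feasibility objective, the recruitment number and the data collection can stand.

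**What to change.** 1. In Sample size, withdraw the 80% claim. Alternatively, restate it as the power of the planned area-level analysis with 3 df over a stated ICC range such as 0 to 0.05, and give the difference and SD that lead to 53 per group.
2. In Analysis, state that EQ-5D-3L and all other between-arm comparisons are exploratory, and report them as estimates with 95% confidence intervals that respect the 3 between-area degrees of freedom.
3. In Secondary outcomes, remove the clause that calls EQ-5D-3L the primary outcome, so that it agrees with the Abstract, Primary outcome and Sample size sections.

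The cost is wording and a less favourable stated power. No extra participants or areas are needed.

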#### Implementation

Initial eligibility screening will be conducted by several RA’s. First by an eligibility screen in the municipality care system, over the phone, and later in the participant’s home. One RA ([name]) will review the study protocol in detail with the potential participant and conducts an eligibility screen in the municipality care system to verify if the individual meets the inclusion or exclusion criteria. Another RA ([name]) will confirm that the participant is interested in participating in the study over the phone. If so, a time will be scheduled to visit the participant’s home. While in the home, a RA will obtain written informed consent from the participant agreeing to participate in the study. If the participant agrees to participate a comprehensive baseline assessment is then obtained to gather outcome measures.

For practical reasons, the intervention cluster will first be included during a period of 10 weeks or until the number needed according to the power calculation and then the control cluster will be included during a period of 10 weeks or until the number needed according to the power calculation.

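### The planned 53 per group does not follow from the printed EQ-5D-3L inputs at 80% power, which give 28–29 or 40–41 per group depending on the SD

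*Protocol article*

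**What the plan says.** All of the inputs stand in one paragraph of the protocol article, under Sample size.

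- **Planning values.** They come from an earlier study described as having the same design, population and outcome. Its EQ-5D-3L follow-up scores are given as "0.758 [0.222] versus 0.534 [0.355"; the bracketed values are not labelled.
- **Clustering.** The variation in quality of life is said to be between individuals and "was not dependent on the clusters". No design effect is applied.
- **Result.** "Hence, with a statistical significance level of 0.05 and a power of 80% app. 53 is needed in each group".
- **Drop-out.** After an allowance of 20%, "app. 130 participants are needed".

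No separate target difference, planning SD or sidedness is given.

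The figure is used again elsewhere. The same section compares the planned size with the samples actually collected, in order to estimate the size of a future trial. Under Analysis, the ICC for quality of life is to be published to judge whether the sample size assessment was appropriate. Under Implementation, each arm recruits for 10 weeks or "until the number needed according to the power calculation".

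**The concern.** The result is introduced as a consequence of the figures just before it. A reader will therefore take 0.224 as the target difference, the bracketed values as SDs and 80% as the power, and expect these to give 53. They do not.

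Assessment of sample size is part of this pilot's primary outcome. If the SD, difference and power behind 53 are unknown or do not match, the pilot's results cannot be set cleanly against the planning calculation. A later planner could not tell whether 53 stands for 80% power for a smaller difference, or for a higher power for 0.224.

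**Working it through.** **Inputs (Sample size section).** Means 0.758 and 0.534, so the difference is 0.758 − 0.534 = 0.224. SDs 0.222 and 0.355 (assumed reading of the brackets). Alpha 0.05 (two-sided assumed). Power 80%. Equal groups. Design effect 1.

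**SD.** Pooled: √[(0.222² + 0.355²)/2] = 0.296. The larger SD, 0.355, is the cautious choice.

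**Attempt to reproduce 53.** Normal formula: n per group = 2(z₀.₉₇₅ + z_power)² SD² / 0.224², with (1.960 + 0.842)² = 7.849 for 80% power and (1.960 + 1.282)² = 10.507 for 90%. The t-based values come from the noncentral t distribution.

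| SD | Power | Normal formula | t-based | Whole numbers |
|---|---|---|---|---|
| 0.296 | 80% | 27.4 | 28.4 | 28–29 |
| 0.355 | 80% | 39.4 | 40.4 | 40–41 |
| 0.296 | 90% | 36.7 | 37.7 | 37–38 |
| 0.355 | 90% | 52.8 | 53.8 | 53–54 |

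The stated 53 is not reproduced at 80% power. It is between 53/41 = 1.3 and 53/28 = 1.9 times what the printed inputs need.

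**Other variants at 80% power.**
- One-sided test: 22–23 (SD 0.296) or 32 (SD 0.355).
- Simple mean of the two SDs, 0.2885: 27–28.
- Smaller SD, 0.222: 16–17.
- Larger SD with an allowance for a Mann-Whitney test (relative efficiency 0.955 or 0.864): 41/0.955 → 43 or 41/0.864 → 48.

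None reaches 53.

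**Could a design effect fill the gap?** It would have to be 53/29 = 1.83 (SD 0.296) or 53/41 = 1.29 (SD 0.355). The section says that the variation did not depend on the clusters, so the text gives no room for one.

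**What 53 per group delivers, ignoring clustering.**

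| SD | Power for 0.224 (t; normal) | Difference detectable at 80% (t; normal) |
|---|---|---|
| 0.296 | 97.1%; 97.3% | 0.163; 0.161 |
| 0.355 | 89.6%; 90.1% | 0.195; 0.193 |

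**What would give 53 at 80% power.** For a difference of 0.224, an SD of about 0.41, which exceeds both printed values. Otherwise, a smaller difference, as in the last column. Neither is stated.

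**Drop-out step.** 53 × 2 = 106, and 106/0.8 = 132.5, against about 130. In the other direction, 130 × 0.8 / 2 = 52 per group.

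**The case against.** The best defence is that the section never calls 0.224 the target difference. It says only that estimates were derived from the earlier study's data. A deliberately smaller target, about 0.16 with SD 0.296 or 0.195 with SD 0.355, would give 53 at 80% power and would be a reasonable planning choice. The article may have condensed that step away. This stands as a possible explanation and limits what can be claimed about the cause. It does not remove the discrepancy, because the article prints inputs, alpha, power and result together and presents the result as following from them.

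It is also fair to say that the pilot's primary outcome is feasibility, that EQ-5D-3L is listed under the secondary outcomes, that the group comparison is exploratory and that the discrepancy is on the safe side. The number is only one of two recruitment limits, the other being 10 weeks. The future trial will also draw on the collected data and the ICC, not on 53 alone. These points stand and lower the severity.

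A reader might infer two stronger things that the document does not support.

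- **That 53 is really a 90%-power figure with the power mislabelled.** This fits only with SD 0.355 in both groups and the normal formula (52.8). The t-based value is 53.8, which rounds up to 54, and the pooled SD needs only 37–38. It is one possible explanation, and a smaller target difference at 80% fits as well.
- **That the drop-out allowance is too small.** Both 53 and 130 are given as approximate. A gap of 2.5 people in the total is rounding, and 52 instead of 53 per group changes power by about half a percentage point (89.0% against 89.6%, t-based, SD 0.355).

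**Conclusion.** The point holds as an arithmetic inconsistency of moderate severity. At 80% power and two-sided 0.05, the printed inputs require 28–29 or 40–41 per group, not 53. For the printed difference, 53 per group gives about 97% or 90% power.

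This rests on three assumptions: the bracketed values are SDs, the test is two-sided, and observations are independent, as the section's own statement on clusters implies. A one-sided test widens the gap.

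The pilot is not underpowered by this discrepancy, since on the individual-level inputs it is larger than 80% power requires. The powers of 97% and 90% should not be read as the power of the cluster-randomised comparison, because they leave clustering out. What suffers is the planning benchmark: its difference, SD and power cannot all be as printed. The document does not show which input differs.

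**What to change.** Keep enrolment at about 130 and reword the Sample size paragraph.

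1. State the target difference, the SD, the sidedness and the power actually used, so that together they give 53 per group. Label the bracketed values.
2. If 0.224 was the target, replace the 80% with the power that 53 per group gives at the named SD: about 90% at 0.355, or about 97% at 0.296.
3. If a smaller difference was the target, state it. At 80% power, 53 per group detects about 0.195 at SD 0.355, or 0.163 at SD 0.296.
4. In either case, say that the figure ignores clustering.
5. Use the restated calculation as the benchmark when the sample size is assessed against the collected data and the ICC.

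The sponsor should report the calculation that was made and not adopt one of these versions because it happens to fit. The cost is one reworded paragraph, with no change to enrolment, assessments or conduct.

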### Randomization

#### Sequence generation

A cluster randomized trial design is used, with community aged care areas, as clusters of randomization. The two clusters were randomly assigned, and it was decided at a above level of the organization in The City of Odense, not knowing about this study, which community aged care areas that should be allocated into the intervention group and the control group. The decision was made in consideration of which community aged care areas was next in having their Health Care Staff participating in the first part of the intervention; the education of the Health Care staff. The prospective participating community aged care areas will be provided with verbal information and full explanation of the trials by an RA ([name]). No written consent form is signed by the community aged care areas.

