**Methods:**

This cluster randomized controlled study will consist of two clusters of a total of 5 community aged care areas; the intervention cluster, which hold 3 community aged care areas and the control cluster which hold 2 areas. The 130 community-dwelling older adults, receiving meals-on-wheels, will randomly be allocated to either the intervention cluster consisting of 8 weeks of participation in a rehabilitation program led by a Case Manager or the control cluster receiving usual community aged care. The primary outcome will be assessment of data collection (ratio between completed- and non-completed data) and assessment of sample size. The secondary clinical outcomes will be health-related quality of life (EQ-5D-3 L), muscle strength (chair stand), nutritional status (weight/BMI), loneliness (UCLA scale), mental well-being (Warwich-Edinburgh scale), self-efficacy (General Self-Efficacy scale), satisfaction with food-related life (SWFL scale) and refrigerator content.

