### Participants

This study will use two sets of eligibility criteria, respectively for the community aged care areas (clusters) and the individual participants.

Community aged care groups (clusters): The citizens who need health care in The City of Odense are placed in a total of five community aged care areas. Excepted are those suffering from severe dementia, brain injury and mental illness, who receive special health care treatment outside the community aged care areas. All five community aged care areas will randomly be assigned into two clusters. The Intervention cluster consists of three community aged care areas: Dalum, Tagtaekker, and Skibhus, and the Control cluster consist of two community aged care areas: Rugaard, and Munkebjerg.

Inclusion and exclusion criteria for the individual participants:Inclusion criteriaCommunity-dwelling older adults (65+ years of age)Receiving meals-on-wheels (at least one time per/week) from the municipal supplier at the time of recruitmentLive in The City of OdenseExclusion criteriaModerate/severe dementia assessed by the community Health Care StaffBeing deaf and/or not understand the language of DanishNot being able to sign the informed consentReceiving (or likely to receive in the next 6 months) enteral tube feeding or parenteral nutrition;Participating in other project in the municipality about nutritional support in the form of dietetic adviceReceiving meals-on-wheels from a private supplier at the time of recruitmentOn an end-of-life care pathway

The reason for exclusion of older adults being deaf or not speaking Danish language is that the project has limited funding for translation into different languages, and it will not be possible to hire a deaf interpreter. It is, however, estimated by the researchers involved, that only a few will be excluded due to this reason.

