#### Allocation concealment mechanism

The allocation will be made based on clusters, which is community aged care areas, rather than individuals. A RA ([name]) from the research group will allocate the individual older adults by pre-recruitment and baseline screening, using a parallel design. The clusters will be identified before randomization of the individual participants. The cluster allocation will be going forward from a list of meals-on-wheels receivers from the municipality kitchen meeting the inclusion criteria within the clusters. Allocation concealment is not possible. After identifying the individual older person, a second RA ([name]), will contact the identified older person by phone for recruitment to the study.

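### Allocation is called random, but the only mechanism described is a municipal decision tied to the staff-education roll-out, so the secondary between-group comparisons cannot be presented as randomised evidence

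*Protocol article*

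**What the plan says.** The protocol article makes three kinds of statement about allocation.

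- **Areas are assigned at random.** Participants: "All five community aged care areas will randomly be assigned into two clusters". The title and Trial design also use the cluster randomised label, and Blinding refers to the results of randomisation.
- **Individuals are randomised.** The abstract says the 130 older adults "will randomly be allocated to either the intervention cluster" or to the control cluster. Allocation concealment mechanism adds: "The clusters will be identified before randomization of the individual participants". That same section also says allocation is by area and not by individual.
- **How it was done.** Sequence generation first says: "The two clusters were randomly assigned, and it was decided at a above level of the organization in The City of Odense". The sentence continues: "not knowing about this study, which community aged care areas that should be allocated into the intervention group and the control group". It then gives the ground for the decision: "The decision was made in consideration of which community aged care areas was next in having their Health Care Staff participating". What these staff were queued for is, as that section identifies it, "the first part of the intervention; the education of the Health Care staff".

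The split is "the intervention cluster, which hold 3 community aged care areas and the control cluster which hold 2 areas". Participants already names the areas in each arm.

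**The concern.** A random label tells the reader that, apart from chance, nothing about the areas determined which arm they entered. The described mechanism gives a different reason: an area's place in the queue for staff education. Because that education is part one of the intervention, areas entered the intervention arm with regard to when they were due to receive a component of it.

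What is at stake is the second aim in the Background, which compares quality of life and muscle strength between involvement in meals and usual care. Sample size is worked out on the between-group EQ-5D-3L difference, and Analysis plans tests and models for group differences. If areas due next for education differ from the others in population, staffing or earlier initiatives, that difference appears in the results as an intervention effect, and the cluster randomised label would lead readers to discount the possibility.

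**Working it through.** No figure in the plan depends on this point, so the check is a reading of the text plus one step of reasoning about the estimate.

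**1. Is a chance process described for areas?** The abstract, Participants and the opening of Sequence generation assert one. None mentions a draw, list, generator or other device. The only mechanism is the municipal decision and its stated ground. That decision settled which areas went to which group, so once it was made nothing remained to be drawn. Count of areas with a described chance process: 0 of 5.

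**2. Is one described for individuals?** The abstract and one sentence of Allocation concealment mechanism say so. The latter section also says allocation is by area, with candidates taken from the municipal kitchen's list of meal recipients within the areas. A person's arm therefore follows from the area where they live. Count of participants with a described chance process: 0 of 130.

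**3. What does this do to the between-group estimate?** Write the outcome of person *i* in area *j* as

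Y_ij = α + β·arm_j + u_j + e_ij,

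where u_j is the area's own level. The expected group difference is

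β + [mean of u over the 3 intervention areas − mean of u over the 2 control areas].

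- Under a true 3:2 draw there are C(5,3) = 10 equally likely allocations. Each area falls in the intervention arm in C(4,2) = 6 of them and in control in the other 4. Averaged over the 10, both means in the bracket equal the overall mean of u, so the bracket averages zero. A single draw may still be unbalanced, but by chance with known probabilities.
- Under roll-out order the 10 allocations have no known probabilities, and nothing makes the bracket average zero. If u is related to place in the queue, the bracket is bias.

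**4. Does the planned model remove the bracket?** Analysis treats the cluster as a random effect. That allows for correlation within areas but assumes u_j is unrelated to arm, which is the assumption in doubt. Arm is constant within an area, so area indicators cannot be added without absorbing arm. Five areas give 5 − 1 = 4 between-area degrees of freedom, and arm uses one, leaving 3. Area-level adjustment is not realistic on that base, and more participants per area do not change it.

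**5. What does not depend on allocation?** The completion ratios under Primary outcome describe how many measurements were obtained. They are valid as descriptions however the areas were chosen.

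**The case against.** Sequence generation itself says the assignment was random, and states that those deciding did not know about the study. The wording is that roll-out order was taken into consideration, which is weaker than saying it determined the choice, and the document does not say how the roll-out order was set. If that order was drawn at random, the label would be right. The comparison is also only exploratory, in a pilot whose primary outcome is feasibility.

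Much of this stands as a limit on the claim. Ignorance of the study makes deliberate selection unlikely, but it supplies no chance element and does not make areas next in line comparable with the rest. The exploratory status limits the harm but does not justify the label on those results.

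A reader might infer more than the document supports:

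- **That there was certainly no random element.** What can be shown is that the label conflicts with the only mechanism described.
- **That the harm is measured by the floor of 1/10 = 0.10 on an exact area-level permutation p-value.** That floor comes from having five areas, applies equally to a genuine draw, and concerns a test the plan does not propose.
- **That control areas had, or would have, the education before follow-up.** The word 'next' invites the question, but the Intervention section places the education in the intervention cluster and gives controls usual care.
- **That the pilot fails because it does not test whether areas can be randomised.** The aims in the Background cover outcome measurement and sample size, not randomisability.
- **That the whole study is undermined.** The completion ratios are not touched.

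**Conclusion.** The point holds as a contradiction between label and mechanism, with a consequence for the secondary results. No chance process is described for any of the five areas or any of the 130 participants, and no other section resolves the conflict. Unless one is documented, the between-group differences in EQ-5D-3L, chair stand and the other clinical outcomes are non-randomised comparisons in which area differences linked to roll-out order cannot be separated from the intervention. The size and direction of any bias cannot be derived, since the document gives no data on how the areas differ.

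This rests on two assumptions: that Sequence generation is a fair account of what happened, and that the roll-out order was administrative and not itself drawn by lot. Evidence against either would settle the matter in the trial's favour.

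**What to change.** First establish whether a genuine chance process was used. If so, describe it in Sequence generation and reconcile it with the account of the roll-out.

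If not:

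1. Replace 'cluster randomised' and 'randomly allocated' with 'non-randomised cluster-controlled pilot' in the title, the abstract, Trial design, Participants, Sequence generation, Allocation concealment mechanism and Blinding.
2. Delete the statements in the abstract and in Allocation concealment mechanism that individuals are randomised.
3. In Analysis, state that between-group differences are exploratory and non-randomised, adjusted for the baseline value of the outcome, age, living alone and meals-on-wheels frequency.
4. State beside those results that the adjustment can reduce imbalance between participants but cannot remove area-level confounding with five areas.

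The cost is rewording and a less favourable design label. The covariates are already collected at baseline, and no extra participants are needed. The primary feasibility analysis stays as planned.
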